#### 2.1.2 Per-Protocol Population

All randomized subjects with no major protocol violations will be included in the Per Protocol (PP) population. The final decisions regarding the PP population will be taken at the Clean File meeting before the database lock.

Major protocol violations will be at least following, but not limited to those:

- Final ROP stage available

|                                     |  |                                    |               |
|-------------------------------------|--|------------------------------------|---------------|
| STATISTISKA KONSULTGRUPPEN          |  | Statistical Analysis Plan          |               |
| Protocol:
Mega Donna Mega |  | Protocol No:
MEGADONNAMEGA 16-7 |               |
|                                     |  | Version:
1.0                    | Page 12 of 21 |

- Compliance to medication will be evaluated for all infants during the treatment period and sub-periods and appropriate cut-off will be applied. The final decision will be made at the clean file meeting before the database lock.

### 2.1.3 Safety Population

All enrolled subjects who received at least one dose of randomized IP will be included in the safety population.

## 3 STUDY VARIABLES

### 3.1 Baseline Variables

#### 3.1.1 Demographics and Baseline Characteristics

Following variables at birth will be summarized for the infant and analysed per treatment group:

- GA
- Sex
- Birth weight (BW) (gram)
- BW standard deviation score (BWSDS) [for infants born GA $\geq$ 24 weeks using reference from Niklasson and Albertsson-Wikland 2008]
- Birth length (BL) (cm)
- BL standard deviation score (BLSDS) [for infants born GA $\geq$ 24 weeks using reference from Niklasson and Albertsson-Wikland 2008]
- Head Circumference (HC) (cm)
- HC standard deviation score (HCSDS) [for infants born GA $\geq$ 24 weeks using reference from Niklasson and Albertsson-Wikland 2008]
- Twin (yes/no)
- Center (Stockholm, Gothenburg, Lund)

Following variables will be summarized for the mother and analysed per treatment group:

- Age (years)
- Parity (number of child in order)
- Mode of delivery
- Diabetes (type 1, 2 or Gestational Diabetes Mellitus [GDM]) (yes/no)
- Preeclampsia (yes/no)
- Other relevant comorbidity (yes/no,specify)

|                                     |  |                                    |               |
|-------------------------------------|--|------------------------------------|---------------|
| STATISTISKA KONSULTGRUPPEN          |  | Statistical Analysis Plan          |               |
| Protocol:
Mega Donna Mega |  | Protocol No:
MEGADONNAMEGA 16-7 |               |
|                                     |  | Version:
1.0                    | Page 13 of 21 |

### 3.1.2 Prior and Concomitant Medications

Medication taken during the pregnancy by the mother will be summarized per treatment group. Given steroids to the infant during the study will be summarized per treatment group. Other medications will be summarized at later stage in another manuscript.

## 3.2 Efficacy Variables

### 3.2.1 Primary Efficacy Variable

Primary efficacy variable in this study is occurrence of sight threatening ROP (ROP stage 3 or worse). All randomized infants will be included in the evaluation of the primary variable. Early drop-outs and deaths before evaluated ROP stage 3 or worse will be considered as non-events and will contribute with their follow-up time in the analysis of comparisons between event rates using Poisson regression. A sensitivity analysis will analyse primary efficacy variable applying survival analyses adjusting for death as competing risk and censoring of those infants that have dropped out due to other reasons than death.

In this study ophthalmologic assessment of ROP stage was performed in blinded manner. Retinal examination were performed approximately once weekly starting at four to five weeks of age according to a standardized protocol and to clinical screening praxis. The evaluation of ROP occurred independently from the study and paediatric ophthalmologists were unaware of which infants were participating in the study.

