### 923 **10.1 Subject Discontinuation**

924 A discontinuation occurs when an enrolled subject ceases participation in the study,  
925 regardless of the circumstances, prior to completion of the protocol.

926

927 The investigator has the right to remove a subject at any time if it is in the best medi-  
928 cal interest of the subject.

929

930 Subjects will be discontinued from treatment prior to completion for any of the fol-  
931 lowing reasons:

932

- 933 • Consent withdrawn / the parents/guardians wish to discontinue study treat-  
934 ment
- 935 • AE (clinical events or laboratory values) that contraindicate continuing the  
936 study.
- 937 • Best interest of the patient, as judged by the Investigator
- 938 • Protocol violation
- 939 • Administrative Decision
- 940 • Other, by Investigator specified reason

941

942 Subjects withdrawn from the study for a SAE should be followed until the SAE has  
943 resolved. Appropriate supportive and/or definitive therapy should be administered as  
944 required.

945

946 The investigator must determine the primary reason for discontinuation. The reason  
947 for a subject discontinuing from the study will be recorded on the case report form.  
948 Withdrawal due to an adverse event should be distinguished from withdrawal due to  
949 other reasons, according to the definition of an adverse event noted earlier. A discon-  
950 tinuation must be reported immediately to UBC Geneva by fax ([contact] or  
951 [contact]) if it is due to a serious adverse event.

952

953 The **End of Study** examination / sampling must be performed at the time of the study  
954 discontinuation. The investigator will record the reason for study discontinuation,  
955 provide or arrange for the appropriate follow-up (if required) for such subject, and  
956 document the course of the subject's condition.

957

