### 3.2.2 Secondary Efficacy Variables

Following secondary efficacy variables will be analysed:

- Postnatal serum fatty acid (in mol%) composition in preterm infants with and without AA:DHA supplementation (at 0h, 72h, day 7, day 14, every second week until PMA of 29 weeks and thereafter at 30, 32, 34, 36, 40 weeks PMA). Missing data will not be imputed, analysis will be performed using Mixed Models for Repeated Measures (MMRM) where missing data at random is assumed.
- Outcome of neonatal morbidities (reported as Adverse Events [AE] from birth to 40 weeks PMA)
  - BPD – this morbidity is evaluated at 36 weeks PMA and will be analysed including the complete ITT population with deaths considered as non-events but their follow-up time will contribute to the total follow-up in the analyses of event rate performed by Poisson regression. Sensitivity analysis of BPD will be performed handling all deaths as endpoint also beside confirmed BPD. Drop-out due to other reasons will be considered as non-event.
  - IVH grade 0-4 – this morbidity is evaluated at an early stage post-birth, and larger amount of missing data is not expected. Drop-outs with missing IVH will be handled as non-events. Sensitivity analysis of IVH will be performed handling all deaths with missing IVH as worst value of this endpoint (?). Drop-out due to other reasons will be considered as non-event. Analyses will be performed using Mantel-Haenszel Chi-square test.
  - PDA - this morbidity is evaluated at an early stage post-birth, and larger amount of missing data is not expected. Drop-outs with missing PDA will be handled as non-events. Sensitivity analysis of PDA will be performed handling all deaths with missing PDA as event (?). Drop-out due to other

|                                     |  |                                    |               |
|-------------------------------------|--|------------------------------------|---------------|
| STATISTISKA KONSULTGRUPPEN   |  | Statistical Analysis Plan          |               |
| Protocol:
Mega Donna Mega |  | Protocol No:
MEGADONNAMEGA 16-7 |               |
|                                     |  | Version:
1.0                    | Page 14 of 21 |

reasons will be considered as non-event. Analyses will be performed using Fisher's Exact test.

- NEC – this morbidity will be analysed in the same way as the primary variable, using Poisson regression in the main and survival analysis in the sensitivity analysis.

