## 4.6 Efficacy Analyses

### 4.6.1 Primary Efficacy Analysis

The primary analysis in this study is incidence of sight-threatening (severe) ROP, i.e. ROP stage 3 or worse. Due to early deaths and early discontinuations in study the primary analysis will be performed using Poisson regression studying event rates, where deaths and early drop-outs are contributing as non-events with their follow-up time in the study. From this analysis Relative Risks (RR) and 95% CI for comparison between the groups will be presented along with the p-value. The primary analysis will be adjusted for stratification used in the randomization, i.e. adjusted for centre and GA categories as fixed effects, according to the guidelines issued by EMA (*Points to consider on adjustment for baseline covariates*).

The main analysis will be performed on ITT population. The sensitivity analysis will be performed on ITT population comparing cumulative incidence rates adjusted for death as

|                                     |  |                                    |               |
|-------------------------------------|--|------------------------------------|---------------|
| STATISTISKA KONSULTGRUPPEN          |  | Statistical Analysis Plan          |               |
| Protocol:
Mega Donna Mega |  | Protocol No:
MEGADONNAMEGA 16-7 |               |
|                                     |  | Version:
1.0                    | Page 18 of 21 |

competing risk, other drop-outs handled as censored in the survival analysis. Gray's test will be performed for this purpose. Moreover, the effect of the sensitivity analysis will be explained by Hazard Ratios (HR) with 95% CI obtained from Cox proportional hazards models. The primary analysis will also be performed on PP population as robustness analysis.

Graphically, cumulative incidence curves with 95% CI will be presented per treatment group.

The analysis will be considered confirmed if the p-value <0.05.

The impact of IP on primary variable will also be evaluated descriptively by centre and by GA categories, used in stratification of the randomization.

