#### 4.6.2 Secondary Efficacy Analyses

Confirmatory analyses of secondary variables:

1. The secondary efficacy analyses of fatty acid levels over time will be evaluated by applying MMRM with the change in level of fatty acids (AA and DHA respectively) from birth as dependent variable, and visit, treatment group as fixed effects, fatty acid at birth as fix adjustment variable, with repeated measures by visit applying the covariance pattern (compound symmetry, autoregressive, Toeplitz, unstructured, overall and applied by treatment group) that minimizes the Akaike's Information Criterion (AIC). From this model without an interaction term the overall effect of the IP will be retrieved, presented by adjusted means with 95% CI. The assumption of normally distributed residuals will be checked by reviewing the diagnostic plots. If not satisfactory the sandwich estimators for the standard errors (resulting in wider CIs) will be applied. Additional model for descriptive (exploratory) purpose will be performed including interaction term from which the impact of IP over time will be retrieved and presented graphically.
2. The secondary efficacy analysis of the impact of IP on BPD will be analyzed on ITT population including infants for which BPD was evaluated at 36 weeks PMA, deaths and other drop-outs will be handled as non-events. Poisson regression with log-link function, will be performed, resulting in RRs with 95% CI and associated p-value.
3. The secondary efficacy analysis of the impact of IP on IVH (grade 0-4) will be analyzed on ITT population using all infants that have evaluated IVH, missing data will be considered as non-events. Mantel-Haenszel Chi-square test will be performed.

Following secondary variables will be analyzed descriptively:

1. PDA will be analyzed using Fisher's Exact test. Proportion of patients with events and 95% CI will be provided.
2. NEC will be analyzed in the same way as the primary efficacy variable, applying Poisson regression. RR with 95% CI will be provided.
3. Growth development, by computing difference with 95% CI between treatment groups in BWSDS, BLSDS, HCSDS for studied time points, only on infants born GA $\geq$ 24 weeks. Individual growth curves will be created by GA week and sex, per treatment group and mean curve estimated per each subgroup of infants.

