## 6 CHANGES OF ANALYSIS FROM PROTOCOL

No changes to protocol version 7b have been done. However, no detailed description of the analyses were available in the protocol. All analyses specified within this SAP are aimed to be conservative regarding the IP and applying ICH and EMA guidelines for statistical analyses and adjustments. Additionally, recently published guidelines from ASA and NEJM have been employed.

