### 2. Clarification on the sensitivity analysis of severe ROP and NEC

**Original definition:** The sensitivity analysis will be performed on ITT population comparing cumulative incidence rates adjusted for death as competing risk, other drop-outs handled as censored in the survival analysis. Gray's test will be performed for this purpose. Moreover, the effect of the sensitivity analysis will be explained by Hazard Ratios (HR) with 95% CI obtained from Cox proportional hazards models.

**Updated definition:** The sensitivity analysis will be performed on ITT population comparing cumulative incidence rates adjusted for death as competing risk, other drop-outs handled as censored in the survival analysis. Gray's test will be performed for this purpose. Moreover, the effect of the sensitivity analysis will be explained by sub-distribution Hazard Ratios (HR) with 95% CI obtained using Fine and Gray method (in order to correspond to the competing risk analysis).

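### No planned analysis of severe ROP counts death as a bad outcome; the primary rate ratio would shift little under unequal deaths, but the competing-risk check would shift more and in the same direction

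*Combined protocol and SAP*

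**What the plan says.** **Severe ROP, main analysis.** SAP 3.2.1: "Early drop-outs and deaths before evaluated ROP stage 3 or worse will be considered as non-events". The same sentence goes on to say that these infants "will contribute with their follow-up time in the analysis of comparisons between event rates using Poisson regression". SAP 4.6.1 repeats the rule: "deaths and early drop-outs are contributing as non-events with their follow-up time in the study".

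**Severe ROP, other analyses.** SAP 4.6.1 plans Gray's test with death as a competing risk and other drop-outs censored. Note-to-SAP 1, item 2, sets the effect measure as "sub-distribution Hazard Ratios (HR) with 95% CI obtained using Fine and Gray method". The per-protocol population (SAP 2.1.2 and the later note that extends it) requires an available final ROP stage.

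**BPD** (fourth in the confirmatory sequence, SAP 4.1). SAP 4.6.2 says "deaths and other drop-outs will be handled as non-events" and names a log-link Poisson model. SAP 3.2.2 and Note-to-SAP 1, item 1, add that follow-up time enters the model. Both also plan a sensitivity analysis in which every death is an endpoint.

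**IVH** (fifth in the sequence). SAP 3.2.2: "Drop-outs with missing IVH will be handled as non-events". Its sensitivity rule, worst grade for deaths with missing IVH, ends in a bracketed question mark. SAP 4.6.2 uses infants with an evaluated IVH, yet scores missing data as non-events.

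**Overall claim.** SAP 6: "All analyses specified within this SAP are aimed to be conservative regarding the IP".

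**The concern.** Protocol 11.1 expects about 15% perinatal deaths. Protocol 8.1 starts retinal examination no earlier than 31 weeks postmenstrual age, so an early death precedes any observable event. If deaths were more frequent with AA:DHA, fewer treated infants would live long enough to show ROP, and the supplement could look protective without being so. One expects the sensitivity analysis to expose this. A competing-risk analysis does not: an infant who dies stays in the subdistribution risk set as never having ROP, so higher mortality lowers cumulative incidence. The per-protocol analysis leaves out infants without a final stage. Death would then show only in the safety tables, away from the efficacy claim.

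Drop-outs raise a smaller form of the same question. Protocol 10.1 says that an end-of-study "examination / sampling must be performed at the time of the study" discontinuation. An examination before the ROP window says nothing about later ROP.

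**Working it through.** **1. The plan's own figure.** Any ROP 42% vs 22%, two-sided 5%, power 80%, unpooled variance: n = (1.960 + 0.842)² × (0.42×0.58 + 0.22×0.78) / 0.20² = 7.849 × 0.4152 / 0.04 = 81.5. This is close to the stated 80 per arm (85 with pooled variance). The calculation is for any ROP. The documents give no severe-ROP rate and no deaths by arm, so both are assumed below.

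**2. Expected deaths.** 0.15 × 105 = 15.75, about 16 per arm if equal.

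**3. Assumptions.** Severe-ROP risk r among survivors is equal in both arms (30% shown; 20% and 40% also checked). Control deaths are 15%. Birth is at about 25.5 weeks, so follow-up to 40 weeks is 14.5 weeks. Events fall on average at 10.5 weeks.

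**4. Formulas**, with d the death proportion and t the week of death:
- Cumulative incidence with death competing: (1−d)r. The ratio is (1−d_T)/(1−d_C) whatever r is.
- Planned person-time rate: (1−d)r / [d·t + (1−d)·S], with S = 10.5r + 14.5(1−r) = 13.3 at r = 30%.
- Severe ROP or death: d + (1−d)r.

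**5. Example, 15% vs 25% deaths.**
- Cumulative incidence: 0.75/0.85 = 0.88.
- Person-time, deaths at week 8: control 0.255/(1.2 + 11.305) = 0.02039; treated 0.225/(2.0 + 9.975) = 0.01879; ratio 0.92.
- Person-time, deaths at week 1: 0.255/11.455 = 0.02226; 0.225/10.225 = 0.02200; ratio 0.99.
- Severe ROP or death: 0.475/0.405 = 1.17.

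Treated vs control ratios at r = 30%:

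| Treated deaths | Cumulative incidence | Person-time, deaths at week 1 / 3 / 8 | Severe ROP or death |
|---|---|---|---|
| 10% | 1.06 | 1.005 / 1.014 / 1.037 | 0.91 |
| 20% | 0.94 | 0.995 / 0.984 / 0.962 | 1.09 |
| 25% | 0.88 | 0.988 / 0.967 / 0.921 | 1.17 |
| 30% | 0.82 | 0.982 / 0.948 / 0.879 | 1.26 |

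With 25% treated deaths, the composite ratio is 1.25 at r = 20% and 1.12 at r = 40%. The first two measures hardly depend on r.

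**6. False positives.** Simulation used 20,000 trials, 105 per arm, deaths uniform over about weeks 0 to 6, and model-based Poisson variance. The chance of a significant result favouring treatment, nominally 2.5%, was:
- Planned rate model: 1.1 to 1.6% with equal deaths, 1.6 to 2.1% with 25% treated deaths, and 2.3 to 2.5% with 30%.
- Plain proportion with deaths as non-events, which is not a planned severe-ROP analysis: 6.0 to 8.7% with 25% treated deaths.

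The model-based variance is already conservative with equal deaths, which is part of the margin. Gray's test was not simulated.

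**7. BPD.** If follow-up time is left out, the ratio at equal survivor risk is again 0.75/0.85 = 0.88. If it is included, as in SAP 3.2.2, the shift is smaller.

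**8. Cost of the composite.** With 15% deaths in both arms and survivor ROP halved from 20%, 30% or 42%, power at 105 per arm is 0.28, 0.50 or 0.75 for severe ROP or death. It is 0.45, 0.65 or 0.84 for ROP with deaths as non-events.

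**The case against.** The strongest defence is the follow-up-time clause. A non-event counted only until exit is in effect censored there, so the primary model is itself a cause-specific rate model and gives a view complementary to Fine-Gray. That stands. It limits the bias to 1 to 8% in the rate ratio under a ten-point death imbalance, and no false-positive inflation was seen. The bias is not removed, because infants who die add event-free time to the denominator, and more of it the later they die.

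Other parts of the defence also stand:
- Non-death drop-outs are censored in the ROP sensitivity analysis.
- Deaths are tabulated as safety (SAP 4.7.2), and withdrawals are broken down by reason and arm (SAP 4.2).
- Nothing says that stopping the supplement ends ROP screening, which runs independently of the study (Protocol 6.3).
- BPD has a firm analysis with death as an endpoint.
- Little missing IVH is expected, and an infant who dies after a scan keeps its grade.

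None of this supplies a severe-ROP analysis in which death counts as unfavourable.

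**Conclusion.** The gap is real and should be fixed, but it does not invalidate the primary test. Under assumed equal survivor risk and 15% vs 25% deaths, the planned rate ratio would be about 0.92 to 0.99, and the cumulative-incidence result behind Gray and Fine-Gray about 0.88. With fewer treated deaths the shift goes the other way. The aim stated in SAP 6 is therefore not assured rather than contradicted.

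A reader might infer more than the documents support:
- That the primary test has inflated type I error. The larger false-positive rates belong to a plain proportion, which is not planned for severe ROP.
- That replacing the Cox model in the Note removed the only cause-specific analysis. The person-time Poisson model is one.
- That deaths will be about as numerous as severe-ROP events. No severe-ROP rate is given.
- That every infant who dies is scored free of IVH. Only missing grades are.

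For BPD the full 0.88 shift arises only if SAP 4.6.2 is read without follow-up time. For IVH the numerical effect is probably small, but the rule contradicts itself and is unfinished.

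**What to change.** 1. **Severe ROP.** Add severe ROP or death before ROP outcome as a named sensitivity analysis of the primary, with deaths by arm beside it. Keep it a sensitivity analysis, because the composite dilutes an ROP-specific effect and loses power. If the data are already locked or unblinded, label it as added afterwards.
2. **Early stoppers.** For infants who stop the supplement or study visits, take the ROP stage from routine screening where consent allows, instead of assuming a non-event.
3. **BPD.** State in SAP 4.6.2 that follow-up time enters the model, as in SAP 3.2.2 and Note-to-SAP 1, item 1. Report the planned death-or-BPD analysis beside the main result. The confirmatory variable need not change.
4. **IVH.** Use evaluated infants only in the main test, give deaths without a scan the worst grade in the sensitivity analysis, and delete the question mark.

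The cost is SAP wording, one added model, a re-run of the IVH test and a look-up of routine ROP results for infants who left early. No new examinations and no change to sample size are needed.

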### 3.2.2 Secondary Efficacy Variables

Following secondary efficacy variables will be analysed:

- Postnatal serum fatty acid (in mol%) composition in preterm infants with and without AA:DHA supplementation (at 0h, 72h, day 7, day 14, every second week until PMA of 29 weeks and thereafter at 30, 32, 34, 36, 40 weeks PMA). Missing data will not be imputed, analysis will be performed using Mixed Models for Repeated Measures (MMRM) where missing data at random is assumed.
- Outcome of neonatal morbidities (reported as Adverse Events [AE] from birth to 40 weeks PMA)
  - BPD – this morbidity is evaluated at 36 weeks PMA and will be analysed including the complete ITT population with deaths considered as non-events but their follow-up time will contribute to the total follow-up in the analyses of event rate performed by Poisson regression. Sensitivity analysis of BPD will be performed handling all deaths as endpoint also beside confirmed BPD. Drop-out due to other reasons will be considered as non-event.
  - IVH grade 0-4 – this morbidity is evaluated at an early stage post-birth, and larger amount of missing data is not expected. Drop-outs with missing IVH will be handled as non-events. Sensitivity analysis of IVH will be performed handling all deaths with missing IVH as worst value of this endpoint (?). Drop-out due to other reasons will be considered as non-event. Analyses will be performed using Mantel-Haenszel Chi-square test.
  - PDA - this morbidity is evaluated at an early stage post-birth, and larger amount of missing data is not expected. Drop-outs with missing PDA will be handled as non-events. Sensitivity analysis of PDA will be performed handling all deaths with missing PDA as event (?). Drop-out due to other

|                                     |  |                                    |               |
|-------------------------------------|--|------------------------------------|---------------|
| STATISTISKA KONSULTGRUPPEN   |  | Statistical Analysis Plan          |               |
| Protocol:
Mega Donna Mega |  | Protocol No:
MEGADONNAMEGA 16-7 |               |
|                                     |  | Version:
1.0                    | Page 14 of 21 |

reasons will be considered as non-event. Analyses will be performed using Fisher's Exact test.

- NEC – this morbidity will be analysed in the same way as the primary variable, using Poisson regression in the main and survival analysis in the sensitivity analysis.
- Postnatal growth development of weight, length, head circumference, at day 0, day 7, day 14, postnatal age (PNA) week 3-7, PMA week 30-40. For infants born at GA $\geq$ 24 weeks SDS will be calculated and summarized per treatment group. Otherwise, for all infants individual growth curves will be created separately by sex and GA week for the two treatment groups. No imputation of missing data is planned.

